## Methods

### Study design

This is a multicenter, open-label, randomized controlled non-inferiority trial with two parallel groups. Two hundred patients with SPLs will undergo EUS-FNB using 22G Franseen needles in 4 tertiary Chinese hospitals and will be randomly assigned to the dry suction group and the wet suction group in a ratio of 1:1. A checklist with the recommendations for Interventional Trials (SPIRIT) is attached as Additional file 1. Study flowchart and standard protocol items displaying the trial’s enrollment, intervention, and assessment schedules were showed in Figs. 1 and 2, respectively.

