### Outcomes

The primary outcome is to compare the rate of diagnostic accuracy of EUS-FNB using the two different suction techniques (dry suction and wet suction). The rate will be calculated as the sum of true positive values and true negative values divided by the total number of samples, with an accurate diagnosis defined as a final diagnosis consistent with the tissue sample obtained during the needle passes.

The secondary outcomes include the optimal number of needle passes, sensitivity, specificity, specimen quality, cytological diagnoses, time of the procedure, and incidence of complications. Specificity analysis is only applicable to participants without malignancy, whereas sensitivity analysis is only applicable to persons with malignancy.

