### Randomization and blinding

Patients will be evaluated by gastroenterologists, surgeons, oncologists, and endoscopists. The potential candidates will be informed and enrolled in this trial by our study team. Stratified blocked randomization was used in the present study. The list of random numbers was generated by an independent statistician who was blinded to this study using the R software (v 4.0.3) by block with stratification on gender. The patients will be allocated randomly to either the dry suction group or the wet suction group in a ratio of 1:1 according to random numbers. To prevent different subject recruitment rates at the various hospitals from interfering in the development of the study, each center will use its list, and the entire population will be randomized in blocks between the two groups.

We used sequentially numbered sealed opaque envelopes to conceal allocation. The cytologists and the pathologists will be blinded during the entire study.

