### Participating sites

All four sites are large tertiary hospitals in China. To avoid biases derived from the learning curve, only the sites with annual EUS-FNA/FNB cases ≧ 100 have been invited to participate in the present study. Endoscopists experienced in interventional EUS, such as EUS-FNA/FNB more than 100 cases, performed the procedures. The Nanfang Hospital of the Southern Medical University is key in minimizing heterogeneity and centralizing decision-making in conflicts. During the conduct of the trial, the principal investigators will monitor the enrollment targets monthly, and the coordination meeting was organized periodically.

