### Cytological and histological analyses

Histopathological diagnosis will be based on cytology or histology. Specimens fixed with formalin will be embedded in paraffin blocks. Immunostaining and nuclear staining will be performed as needed. Experienced pathologists who have performed at least 1000 cytology and histology evaluations of EUS-FNA/B specimens will assess the specimens independently. The pathologists will be blinded to the allocation.

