### Final diagnosis

The malignant diagnosis was defined as the cytological or pathological diagnosis considered suspicious or positive for malignancy. Neuroendocrine tumors, solid pseudopapillary neoplasm, lymphoma, and melanoma were also considered to be malignant lesions.

The final diagnostic standards are as follows:For patients who undergo surgery, the final diagnosis will be based on the definite evidence of malignancy from surgical specimens.For patients who did not receive surgery, the final diagnosis will be considered as malignancy if cytologic or histologic diagnosis of malignancy is made by EUS-FNB with a corresponding clinical manifestation.For patients with negative or unsatisfactory pathological results, the final diagnosis will be confirmed by clinical and imaging follow-up for 1 year. If there was no imaging progression of the SPL, the true negative would be considered, and if there was progression or death, the false negative would be determined.

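### In an open-label trial, masking is stated for the biopsy readers but not for whoever sets the follow-up-based final diagnosis of unoperated patients, and a few such calls can decide non-inferiority

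*Protocol article*

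**What the plan says.** The protocol article, under Study design, states: "This is a multicenter, open-label, randomized controlled non-inferiority trial with two parallel groups". Under Randomization and blinding it lists who is masked: "The cytologists and the pathologists will be blinded during the entire study". The section on cytological and histological analyses repeats this for one of the two roles: "The pathologists will be blinded to the allocation". No other role is named as masked.

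Under Outcomes, the primary endpoint is diagnostic accuracy (true positives plus true negatives over all samples), with "an accurate diagnosis defined as a final diagnosis consistent with the tissue sample obtained during the needle passes".

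The Final diagnosis section gives three routes to the reference standard:

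- **Operated patients:** "the final diagnosis will be based on the definite evidence of malignancy from surgical specimens".
- **Unoperated patients with a positive biopsy:** malignant "if cytologic or histologic diagnosis of malignancy is made by EUS-FNB with a corresponding clinical manifestation".
- **Negative or unsatisfactory biopsy:** "the final diagnosis will be confirmed by clinical and imaging follow-up for 1 year". Absence of progression on imaging makes a true negative; progression or death makes a false negative.

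The section gives no criterion for progression or for a matching clinical picture. The Discussion confirms that surgical pathology will not be available for every patient. Under Participating sites, the lead hospital is described as "key in minimizing heterogeneity and centralizing decision-making in conflicts".

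**The concern.** Accuracy is an agreement between two readings, and the stated masking protects one of them. Masking the pathologists does nothing for a call made a year later from scans and clinical course. In an unoperated patient with a negative biopsy, calling the lesion stable scores the biopsy as correct, and calling it progressive scores it as an error. If the person making that call knows the suction technique, classification can depend on the arm, and the primary difference is then biased directly.

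The planned accuracies are close to 100%, so each arm is expected to produce very few errors. A small number of arm-dependent calls could therefore produce a false claim of non-inferiority or prevent a true one.

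**Working it through.** **Inputs** (protocol article, Sample size calculation): accuracy 96.2% dry and 98.3% wet, margin 10 points, α = 0.025, power 90%, allocation 1:1, 180 evaluable, 200 with 10% dropout.

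**1. The plan's own figure.** With one-sided α = 0.025,

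n per arm = (1.960 + 1.282)² × [0.962 × 0.038 + 0.983 × 0.017] / (0.10 − 0.021)² = 89.7, so 90.

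That gives 180 evaluable, and 180 / 0.90 = 200. Both figures reproduce. Masking the final diagnosis does not change them.

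**2. Expected errors at 90 per arm.** Dry: 90 × 0.038 = 3.4. Wet: 90 × 0.017 = 1.5. One reclassified patient moves an arm's accuracy by 1/90 = 1.1 points.

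**3. Where the conclusion turns.** Assume non-inferiority is declared when the lower 97.5% limit of dry minus wet lies above −10 points. Two limits are shown as a range:

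- Wald: d − 1.96 × √[p_D(1 − p_D)/90 + p_W(1 − p_W)/90]
- Newcombe: d − √[(p_D − l_D)² + (u_W − p_W)²], where l_D and u_W are Wilson limits.

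Example with 5 dry and 1 wet error: d = −4/90 = −4.44 points, standard error 2.66 points, Wald limit −9.65.

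| Wet errors | Dry errors | Wald limit (points) | Newcombe limit (points) |
|---|---|---|---|
| 1 | 4 | −8.11 | −9.83 |
| 1 | 5 | −9.65 | −11.30 |
| 1 | 6 | −11.15 | −12.74 |
| 2 | 4 | −7.46 | −8.85 |
| 2 | 5 | −8.96 | −10.32 |
| 2 | 6 | −10.43 | −11.75 |

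By Wald, non-inferiority holds at 5 dry errors and fails at 6. By Newcombe it holds at 4 and fails at 5. At 100 per arm the turning point is the same with 1 wet error and one dry error higher with 2.

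**4. Relabelling in favour of dry suction.** Take dry truly at the margin (88.3% against 98.3%, 90 per arm). Enumerate both binomial distributions exactly and count k dry errors as correct. The range of k is an assumption.

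| k | False non-inferiority, Wald | False non-inferiority, Newcombe |
|---|---|---|
| 0 | 4.6% | 2.2% |
| 1 | 9.3% | 5.0% |
| 2 | 16.6% | 9.9% |
| 3 | 26.6% | 17.3% |

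**5. Relabelling against dry suction.** At the planned accuracies, 0, 1, 2 or 3 extra dry errors take the exact Wald power from 85.9% to 72.9%, 54.5% and 33.7%.

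**The case against.** The strongest reply is that the concern rests on silence. The article does not say who reads the follow-up scans or assigns the final diagnosis, or that these people know the arm. The full protocol might name a masked reader. This stands as a limit on the claim: the text shows an unprotected step, not an actual bias. It does not dispose of the point, because the article does state who is masked, and its list stops at cytologists and pathologists.

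Three stronger readings are tempting, and the documents do not support them.

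- **That the final diagnosis as a whole rests on clinical and imaging judgement.** It does not. Operated patients are settled by the specimen, deaths are objective, and an unoperated positive rests mainly on the masked pathology reading. The clearly exposed group is unoperated, alive and biopsy-negative or unsatisfactory, with borderline imaging. The article gives no count of it.
- **That the bias would favour dry suction.** The Discussion's expectation that dry suction will match wet suction is offered as the reason for a non-inferiority design. It is not evidence of how assessors would lean.
- **That a few calls in favour of dry suction would change the result at the planned accuracies.** They would not. With 4 dry errors and 1 or 2 wet errors non-inferiority already holds, and moving dry errors to correct leaves it so. Relabelling in that direction does harm when dry is truly worse (step 4); at the planned rates, the harm comes from added dry errors (step 5).

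Also, the 3.4 and 1.5 expected errors are all errors, and not all of them would be open to judgement.

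**Conclusion.** The point holds for unoperated patients: those with a negative or unsatisfactory biopsy, whose true or false negative status comes from one-year follow-up, and to a lesser degree those with a positive biopsy, where a clinical judgement contributes. No masking is stated for either call. It is a risk of bias whose direction and size the article does not allow one to determine.

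The arithmetic shows that the result is sensitive to small numbers. The conclusion turns on a single dry error between 5 and 6 (Wald) or between 4 and 5 (Newcombe), and relabelling three dry errors in a truly inferior arm multiplies the false non-inferiority rate about sixfold (26.6 / 4.6 = 5.8) or eightfold (17.3 / 2.2 = 7.9). This rests on 90 evaluable per arm, 1 or 2 wet errors for the turning point, a decision by the lower 97.5% limit, and an assumed 0 to 3 relabelled cases. The plan should be changed, but the point is not proof that the result will be biased.

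**What to change.** State in the protocol and analysis plan that, for unoperated patients:

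- the progression call and the final diagnosis are made by existing study staff who neither performed nor attended the procedure and do not know the suction arm. Lead-centre staff can serve only if they meet this condition;
- they work from follow-up images or reports and clinical data with the suction technique removed, and make the progression call themselves instead of adopting an unmasked site judgement;
- they use a progression criterion written down in advance;
- the classification is locked before allocation is merged.

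Apply this to every classification still to come. The Trial status section gives 123 enrolled by October 2023 and recruitment to June 2024, so at that date 200 − 123 = 77 patients had not yet been enrolled. Recruitment began in September 2022, so some one-year calls may already exist. Re-classify those under masking from existing records, and report how many were originally made unmasked. If masking of this kind is already in place, stating it in the protocol, together with the progression criterion, is enough.

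The cost is administrative: masking and forwarding follow-up records. It needs no new assessors, visits or patient procedures, and the sample size stays at 180 evaluable and 200 enrolled.

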### Participating sites

All four sites are large tertiary hospitals in China. To avoid biases derived from the learning curve, only the sites with annual EUS-FNA/FNB cases ≧ 100 have been invited to participate in the present study. Endoscopists experienced in interventional EUS, such as EUS-FNA/FNB more than 100 cases, performed the procedures. The Nanfang Hospital of the Southern Medical University is key in minimizing heterogeneity and centralizing decision-making in conflicts. During the conduct of the trial, the principal investigators will monitor the enrollment targets monthly, and the coordination meeting was organized periodically.

### EUS-FNB procedure

Patients will be assigned to group A (dry suction) or group B (wet suction). In both groups, we will use the 22G Franseen needle (Acquire™, Boston Scientific) to puncture the SPLs.

All procedures will be conducted by doctors with experience in more than 100 cases of EUS-FNA/FNB before the start of the study. During the procedure, the needle was moved back and forth about 10–20 times using the fanning method as much as feasible. Standard negative pressure with a 10-mL syringe was applied in both groups.

### Dry suction

In the dry group, before puncturing the lesion, the stylet is removed, and a 10-ml air-filled pre-vacuum syringe is attached. The needle is moved back and forth about 10–20 times within the lesion using a fanning technique. Afterward, the needle is withdrawn from the lesion.

### Wet suction

With the use of the wet suction technique, the stylet will be removed from the needle before puncture; the needle will then be flushed with 5 mL of saline to replace the column of air with fluid. After the needle punctures the lesion, a 10-mL air-filled syringe will be attached to the end of the needle to provide continuous negative pressure suction while the needle is moved back and forth.

### Post-trial care

In the postoperative period, we will make a 72-h follow-up to monitor any postoperative adverse events. The participants will be compensated with $100 when they finish the trial and follow-up.

### Specimen

After 3 needle passes, the doctor will evaluate the adequacy of the sample with macroscopic on-site evaluation (MOSE) and decide whether to continue additional punctures. MOSE was performed by gross visualization of the collected material by the endoscopists and considered adequate when a white/yellowish aggregate core longer than 10 mm was retrieved. Three needle passes at least were required for both groups. The specimens obtained at each pass will be marked and sent to pathology separately. It is to be evaluated using traditional cytological smear, liquid-based thin layer cytological examination, and histological examination for each pass.

### Cytological and histological analyses

Histopathological diagnosis will be based on cytology or histology. Specimens fixed with formalin will be embedded in paraffin blocks. Immunostaining and nuclear staining will be performed as needed. Experienced pathologists who have performed at least 1000 cytology and histology evaluations of EUS-FNA/B specimens will assess the specimens independently. The pathologists will be blinded to the allocation.

### Final diagnosis

The malignant diagnosis was defined as the cytological or pathological diagnosis considered suspicious or positive for malignancy. Neuroendocrine tumors, solid pseudopapillary neoplasm, lymphoma, and melanoma were also considered to be malignant lesions.

The final diagnostic standards are as follows:For patients who undergo surgery, the final diagnosis will be based on the definite evidence of malignancy from surgical specimens.For patients who did not receive surgery, the final diagnosis will be considered as malignancy if cytologic or histologic diagnosis of malignancy is made by EUS-FNB with a corresponding clinical manifestation.For patients with negative or unsatisfactory pathological results, the final diagnosis will be confirmed by clinical and imaging follow-up for 1 year. If there was no imaging progression of the SPL, the true negative would be considered, and if there was progression or death, the false negative would be determined.

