### Sample size calculation

The sample size calculation was based on the primary outcome of diagnostic accuracy for the evaluation of solid pancreatic lesions. The reported diagnostic accuracy of EUS-FNB for SPL using dry suction is approximately 96.2%, and the wet suction technique is about 98.3% in the literature [6, 8]. Based on the reported data and the clinical judgment, the non-inferiority of dry suction in EUS-FNB will be assessed with a non-inferiority (*δ*) margin of 10%. With a two-sided test, a significance level of 2.5% (*α* = 0.025), and a power (1 − *β*) of 90%, using the PASS 15.0 software and a sample allocation ratio of 1:1 between the dry suction and wet suction groups, 180 patients should be enrolled. Considering a 10% dropout rate, a final sample of 200 participants (100 per group) is needed.

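### An unsatisfactory biopsy in an unoperated patient whose lesion is stable at 1 year is scored as an accurate diagnosis in the primary endpoint

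*Protocol article*

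**What the plan says.** Three statements in the protocol article combine.

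- **Outcomes, formula.** "The rate will be calculated as the sum of true positive values and true negative values divided by the total number of samples".
- **Outcomes, definition.** The same sentence goes on with "an accurate diagnosis defined as a final diagnosis consistent with the tissue sample obtained during the needle passes".
- **Final diagnosis, third standard.** "For patients with negative or unsatisfactory pathological results, the final diagnosis will be confirmed by clinical and imaging follow-up for 1 year". The next sentence assigns the labels. For stable lesions it reads: "If there was no imaging progression of the SPL, the true negative would be considered". A patient who progresses or dies is labelled a false negative instead.

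Patients who have surgery take their final diagnosis from the surgical specimen. Unoperated patients with a malignant EUS-FNB reading and a matching clinical picture are final malignancies. The third standard therefore governs negative and unsatisfactory results in unoperated patients. The article has no separate non-diagnostic category.

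**The concern.** A negative reading is a diagnostic statement that follow-up can confirm or refute. An unsatisfactory sample makes no statement. Once the two are pooled, a failed biopsy in a patient with a benign or slow-growing lesion enters the numerator of the primary endpoint as a success.

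Two consequences follow. Accuracy is overstated in each arm that has such patients, and so is specificity, which is calculated among patients without malignancy. If the arms differ in how often sampling fails, part of that difference also disappears from the primary comparison. In a non-inferiority trial, a rule that can hide failures of the test technique (dry suction) matters more than it would in a superiority trial.

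The same sentence has a secondary problem. Any death within the year turns a negative or unsatisfactory result into a false negative, whatever the cause, in a population eligible up to age 85. A correct benign reading followed by an unrelated death is then scored as a diagnostic miss.

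**Working it through.** **1. The plan's own figure.** Sample size calculation gives 96.2% (dry), 98.3% (wet), a 10-point margin, α = 0.025, 90% power and 1:1 allocation. With unpooled variance and α taken as one-sided:

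n per arm = (1.960 + 1.282)² × (0.983 × 0.017 + 0.962 × 0.038) / (0.10 − 0.021)² = 10.507 × 0.053267 / 0.006241 = 89.7, rounded up to 90.

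That is 180 in total, and 180 / 0.90 = 200. The stated sample size reproduces, so the point does not rest on a sample size error.

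**2. The rule applied to the formula.**

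| EUS-FNB result, unoperated patient | At 1 year | Label under Final diagnosis | Counted in Outcomes as |
|---|---|---|---|
| Negative, satisfactory | stable | true negative | accurate |
| Negative, satisfactory | progression or death | false negative | not accurate |
| Unsatisfactory | stable | true negative | **accurate** |
| Unsatisfactory | progression or death | false negative | not accurate |

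Only the third row is at fault. Each such patient adds 1/90 = 1.1 points to an arm of 90. The planned arm difference is 98.3 − 96.2 = 2.1 points.

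**3. Effect on the arm difference.** Let u be the unsatisfactory rate in an arm and s the share of those patients who are unoperated and stable. Let A be accuracy with unsatisfactory samples counted as failures. The rule scores A + u·s, so

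scored gap (wet − dry) = true gap − (u_dry − u_wet) × s.

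The gap narrows if dry fails more often, is unchanged at equal rates, and widens if wet fails more often.

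**4. Effect on the error rate.** *Assumptions, none of them in the documents:* true accuracy 88% dry v 98% wet (a gap exactly at the margin), 90 analysed per arm, non-inferiority declared when the lower limit of the 95% Newcombe interval for dry minus wet is above −10 points, and s the same in both arms. Exact binomial enumeration gives 2.2% when unsatisfactory samples count as failures. Under the written rule:

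| Unsatisfactory, dry v wet | s = 10% | s = 25% | s = 50% |
|---|---|---|---|
| 2% v 2% | 2.2% | 2.2% | 2.1% |
| 2% v 1% | 2.3% | 2.5% | 2.9% |
| 5% v 1% | 2.8% | 3.9% | 6.9% |
| 8% v 1% | 3.3% | 6.0% | 15.0% |

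Worked cell, 8% v 1% at s = 50%: dry 88 + 8 × 0.5 = 92.0%; wet 98 + 1 × 0.5 = 98.5%; the scored gap is 6.5 points against a true 10.

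Reverse case, 1% dry v 2% wet at s = 50%: dry 88.5%, wet 99.0%, scored gap 10.5 points. Here the rule works against non-inferiority.

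**The case against.** **The consistency wording in Outcomes may already exclude these cases.** An unsatisfactory sample has nothing for a final diagnosis to agree with, so a careful reader could refuse to call it accurate. This stands as far as showing a conflict. It does not resolve it: Final diagnosis is the specific rule that assigns the labels, it names unsatisfactory results, and Outcomes counts every true negative.

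**Few patients can be affected.** A patient must be unsatisfactory across all passes, unoperated and stable. The Specimen section requires at least three passes, macroscopic on-site evaluation after the third, and smear, liquid-based cytology and histology on each pass. The planning accuracies ("The reported diagnostic accuracy of EUS-FNB for SPL using dry suction is approximately 96.2" per cent, and "the wet suction technique is about 98.3% in the literature") leave about 4% and 2% for errors and failures together. This stands, and it makes the lower rows of the table less likely than the upper ones. The plan nevertheless provides for unsatisfactory results, and one patient moves an arm by half the planned difference.

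**Stronger readings that the documents do not support.**

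- A reader might infer that the rule biases the trial towards non-inferiority. That needs dry suction to fail more often. Background cites better adequacy with wet suction for aspiration needles, but Discussion reports conflicting biopsy-needle studies, one with no significant difference in specimen quality.
- A reader might infer that adequacy is the main way in which the techniques differ. The article does not say so, and specimen quality is a separate secondary outcome, so a difference there would still be reported.
- A reader might take 15% as the size of the problem. It is the extreme cell of an assumed grid.
- A reader might rank the death clause equally. It applies the same rule to both arms, covers only negative or unsatisfactory results, lowers accuracy, and cannot be quantified from the documents.

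**Conclusion.** The rule is wrong as written. Followed literally, it scores a failed biopsy as an accurate diagnosis in unoperated patients with stable lesions, and it contradicts the article's own definition of accuracy. That conclusion rests on the text alone.

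The size is uncertain because the article gives neither an unsatisfactory rate nor a stable share. In the grid above, the effect on false non-inferiority runs from nil at equal failure rates to 15.0% at the far corner. Most cells with unequal rates lie between 2.3% and 6.9%. The direction depends on which technique fails more often; the overstatement of accuracy does not. The all-cause death clause is a real but secondary misclassification.

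**What to change.** 1. In the primary endpoint, score an unsatisfactory or non-diagnostic EUS-FNB as not accurate, whatever the follow-up shows.
2. Reserve the true-negative label for a satisfactory sample with a negative or benign reading that follow-up confirms, and align the Outcomes and Final diagnosis sections.
3. Report the present rule as a sensitivity analysis.
4. Add a sensitivity analysis in which deaths within 1 year that are judged, blind to arm, to be unrelated to the pancreatic lesion leave the final diagnosis undetermined.

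**Cost.** This is mainly a change of endpoint wording. Pathology results for each pass and 1-year follow-up are already collected; the only added work is blinded review of a few deaths. Trial status reports 123 of 200 patients enrolled in October 2023, so at that point the change could still be made by amendment. It should be fixed before any comparison by arm.

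Measured accuracy will be slightly lower in both arms. The article does not say whether its planning accuracies counted unsatisfactory samples as failures. If they did, planning is unaffected. If they did not, power should be rechecked: one patient fewer per arm (97.2% v 95.1%, same 2.1-point gap) lowers power at 90 per arm from 90.1% to 78.7% by the formula in step 1.

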Second, surgical pathological data was not available in all patients with SPLs. Some patients do not undergo surgery because the lesion is benign or because they refuse surgical treatment. Thus, clinical and imaging follow-up will be done for at least 12 months to determine the final diagnosis.

In conclusion, this is the first multicenter randomized controlled trial designed to clarify whether the dry suction technique is non-inferior to the wet suction technique and the optimal needle passes for SPLs using a 22G Franseen needle. The findings may provide high-level evidence of EUS-FNB procedures in clinical practice.

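### The one-year rule for negative biopsies makes absence of imaging progression the only stated true-negative test, and does not say how to score cancer proven by other non-surgical tissue or kept stable by treatment

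*Protocol article*

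**What the plan says.** The Final diagnosis section of the protocol article has three parts.

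- **Surgery:** "For patients who undergo surgery, the final diagnosis will be based on the definite evidence of malignancy from surgical specimens".
- **No surgery:** the final diagnosis is malignant "if cytologic or histologic diagnosis of malignancy is made by EUS-FNB with a corresponding clinical manifestation".
- **Negative or unsatisfactory result:** "For patients with negative or unsatisfactory pathological results, the final diagnosis will be confirmed by clinical and imaging follow-up for 1 year". Two outcomes follow. The favourable one reads "If there was no imaging progression of the SPL, the true negative would be considered". The unfavourable one, which covers any death as well as growth of the lesion, reads "if there was progression or death, the false negative would be determined".

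The same section widens the malignant class: "Neuroendocrine tumors, solid pseudopapillary neoplasm, lymphoma, and melanoma were also considered to be malignant lesions".

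The Outcomes section defines the primary endpoint, diagnostic accuracy, as "the sum of true positive values and true negative values divided by the total number of samples". It restricts sensitivity to patients with malignancy and specificity to those without. The Discussion says of patients without surgical pathology that "clinical and imaging follow-up will be done for at least 12 months to determine the final diagnosis".

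**The concern.** A reference standard should use the best evidence available on each patient. Here, once a study biopsy is negative and there is no surgery, the only stated route to a true negative is that the lesion did not progress on imaging. Suppose the biopsy misses a cancer, a node or metastasis biopsy then proves it, and treatment holds the primary lesion stable. That patient meets the stated true-negative test, so the missed cancer enters the primary endpoint as a correct diagnosis. The patient also moves from the sensitivity denominator to the specificity denominator.

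In a non-inferiority trial this matters beyond the absolute accuracy figure. Turning the same share of misses into correct results in both arms narrows any real gap between the techniques, which makes a non-inferiority claim easier to reach.

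**Working it through.** **1. Which patients the text settles**

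| Negative study biopsy, then | What the text gives |
|---|---|
| Cancer found at resection | Settled by the surgical specimen, if that part takes precedence. The follow-up part is not limited to unoperated patients and no order is stated. |
| Malignant repeat EUS-FNB, lesion stable | Malignant under the second part if a repeat counts; true negative under the third part. The text does not choose. |
| Cancer proven by node, metastasis or percutaneous biopsy, lesion stable | No part accepts this tissue. Literal result: true negative. |
| Anticancer treatment, lesion stable, no further tissue | Treatment is not mentioned. Literal result: true negative. |
| Untreated neuroendocrine tumour or solid pseudopapillary neoplasm, stable at one year, no further tissue | True negative, although the section counts these tumours as malignant. |
| Progression or death, no evidence of malignancy | False negative. This errs in the opposite direction. |

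**2. The plan's own sample size, as a starting point**

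Inputs from Sample size calculation: dry 96.2%, wet 98.3%, margin 10 points, alpha 0.025, power 90%, 1:1 allocation. With alpha taken as one-sided (z = 1.960 and 1.2816) and unpooled variance:

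n per arm = (1.960 + 1.2816)² × (0.983×0.017 + 0.962×0.038) / (0.10 − 0.021)² = 10.51 × 0.05327 / 0.006241 = 89.7, so 90 per arm and 180 in total; 180/0.9 = 200.

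The stated figure is reproduced. It does not decide the present point, but it gives the 90 per arm used below.

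**3. Effect of re-scoring on the difference**

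Let W and D be the true wet and dry accuracies, and let a share f of the errors in each arm be scored as true negatives. The observed accuracies are D + f(1 − D) and W + f(1 − W), so

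observed difference = (D − W)(1 − f).

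With W = 98.3% and D = 88.3% (a true deficit of exactly the margin), the observed deficit is 10.0 points at f = 0, 9.0 at f = 0.1 and 8.0 at f = 0.2.

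**4. Effect on the false-claim rate (illustration)**

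Assumptions: 90 per arm, Farrington-Manning test of the 10-point margin at z = 1.96, exact enumeration over two binomials. Error rates are 11.7%×(1 − f) for dry and 1.7%×(1 − f) for wet.

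| f | Observed accuracy, dry / wet | Probability of a false non-inferiority claim |
|---|---|---|
| 0 | 88.3% / 98.3% | 2.2% |
| 0.1 | 89.5% / 98.5% | 3.9% |
| 0.2 | 90.6% / 98.6% | 6.9% |

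The documents give no value of f.

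**5. Scale at the planned accuracies**

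Expected errors are 90 × 0.038 = 3.4 in the dry arm and 90 × 0.017 = 1.5 in the wet arm, about 5 in 180 patients. At f = 0.2, about one patient is re-scored (4.95 × 0.2 = 0.99).

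**The case against.** The strongest reply is that the text is silent on later proof of cancer; it does not tell assessors to ignore it. A reader might infer that any negative biopsy becomes a true negative whenever the lesion is stable, even when cancer has since been proven. The documents do not support that. A resected cancer is meant to be settled by the specimen, and a malignant repeat EUS-FNB can reasonably be read into the second part. The follow-up is described as clinical as well as imaging, so an assessor might well take later proof into account. Precedence and the handling of treated lesions may also stand in the full protocol behind this article.

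A reader might also infer that reported accuracy must be too high. That is not shown either, because growth of a benign mass and death from any cause are both scored as misses.

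The illustration can be challenged too. It assumes a true dry accuracy of 88.3% against the planned 96.2%. Only a patient who is unoperated, has a missed cancer, is alive and shows no progression at one year can be re-scored, so large values of f have no support in the documents. The Discussion also acknowledges that surgical pathology will not be available for everyone.

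These points narrow the concern but do not remove it. The true-negative sentence is an operative rule in the current text, and it names imaging alone. Followed as written, it misclassifies cancers proven by other tissue and makes no allowance for treatment. For a malignant repeat EUS-FNB it lets two centres score the same patient differently.

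**Conclusion.** The point holds in a limited form and should be fixed. The stated true-negative test gives a wrong result for malignancy proven by non-surgical tissue other than EUS-FNB in a lesion that stays stable, and it can do so for cancers held stable by treatment. The status of a repeat EUS-FNB and the order of the three parts are left open.

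Such re-scoring at an equal share in both arms reduces the true difference by the factor (1 - f), towards non-inferiority. The false-claim rates of 3.9% and 6.9%, against 2.2% with no re-scoring, depend on assumed values of f and on a true deficit placed at the margin. They show direction and sensitivity and do not estimate what will happen in this trial. At the planned accuracies the number of patients affected may be very small, but so is the expected number of errors. The net bias in absolute accuracy is not established.

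**What to change.** State an order of precedence in the Final diagnosis section.

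1. Any tissue diagnosis of malignancy of the index lesion during follow-up (surgery, repeat EUS-FNB or another biopsy) sets the final diagnosis to malignant and overrides the imaging rule. The negative study biopsy is then a false negative.
2. Without such tissue, no progression over at least 12 months is a true negative only if no anticancer treatment was given for the lesion.
3. All remaining patients (treated and stable without tissue, or progressing without documented malignancy) are classified by one pre-specified rule, applied blind to arm. They stay in the primary analysis, and a sensitivity analysis scores them the other way. This step is needed because the Statistical analysis plan section deletes missing data, so patients left unclassified could drop out of the primary analysis.

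Record later tissue results and anticancer treatment at the planned one-year follow-up, and apply the rule from records to patients already enrolled (123 by October 2023, according to Trial status).

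The cost is protocol wording and one or two CRF items, with no extra procedures. Reported accuracy may be slightly lower. Untreated indolent tumours that never yield tissue remain unresolved and should be acknowledged as a limitation.
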